# Peer-driven intervention to help patients resume CPAP therapy following discontinuation: a multicentre, randomised clinical trial with patient involvement

**DOI:** 10.1136/bmjopen-2021-053996

**Published:** 2021-10-14

**Keywords:** respiratory medicine (see thoracic medicine), sleep medicine, chronic airways disease

## Abstract

**Introduction:**

Obstructive sleep apnoea syndrome (OSAS) is one of the most common chronic diseases. It may be associated with symptoms of excessive daytime sleepiness and neurocognitive and cardiovascular complications. First line therapy for OSAS involves home continuous positive airway pressure (CPAP), however, nearly half of patients do not adhere with this treatment over the long term. Cognitive-behavioural interventions that include health professionals and patient and public involvement are increasingly advocated in the fields of education and research. We hypothesise that a peer-driven intervention could help patients with OSAS to resume CPAP use after discontinuation.

**Methods and analysis:**

We have designed a prospective, multicentre randomised, controlled trial that will be coconducted by health professionals, a home provider of CPAP and patients as experts or peers or participants. The primary aim is to evaluate the impact of a 6-month, peer-driven intervention to promote the resumption of CPAP after discontinuation. We anticipate that 20% of patients in the intervention group will reuse CPAP as compared with 6% in control group, thus, 104 patients must be included in each group. The secondary aims are (1) to evaluate the impact of the peer-driven intervention on adherence to CPAP compared with the control group (mean adherence and percentage of nights with at least 4 hours’ use/night for 70% of nights); (2) to determine factors associated with resumption of CPAP; (3) to assess patient satisfaction with the peer-driven intervention at 6 months; (4) to evaluate the feasibility and the execution of the peer-driven intervention and peer satisfaction. Adult outpatients with an established diagnosis of severe OSA (Apnoea-Hypopnoea Index >30 events/hour) that have stopped using CPAP within 4–12 months after initiation will be recruited. The peers who will perform the intervention will be patients with OSAS treated with CPAP with good adherence (at least 4 hours/night, 70% of nights) and trained in motivational enhancement and cognitive-behavioural therapies. Trained peers will conduct three interviews within 6 months with participants.

**Ethics and dissemination:**

Ethical approval has been obtained from the French Regional Ethics Committee CPP Ouest II-Angers, (IRB 21.02.25.68606 (2021/2025)). All participants will sign written informed consent. The results will be presented at conferences and published in peer-reviewed journals as well as public media.

**Trial registration number:**

NCT04538274

Strengths and limitations of this studyPatient involvement from the beginning of the setup of this trial.There is a rationale supporting the use of motivational enhancement and cognitive-behavioural therapies performed by peers to promote continuous positive airway pressure resumption.Our team has experience in patient and public involvement from work undertaken at the Grenoble Alpes University Department of Patients.Challenges are to train enough peers with homogeneous skills.

## Introduction

Obstructive sleep apnoea syndrome (OSAS) is one of the most common chronic diseases. It is characterised by recurrent episodes of upper airway collapse during sleep, and may or may not be associated with symptoms of excessive daytime sleepiness (EDS) and neurocognitive and cardiovascular complications.^1^ Twelve million adults aged between 30 and 69 years may have moderate to severe OSAS in France, based on an Apnoea–Hypopnoea Index (AHI) threshold value of 15 or more events per hour of sleep.^2^ The risks associated with the disease can be severe, for example, individuals with untreated OSAS have a three times greater risk of motor vehicle accidents than the general population.^3^ OSAS is also associated with an increased risk of cardiovascular disease, diabetes and glucose dysregulation,^4^ independent from obesity.^5^

The first line therapy for OSAS is continuous positive airway pressure (CPAP).^1 6 7^ CPAP has been shown to effectively reduce EDS and to improve daily functioning, cognitive function, mood and quality of life.^3 6^ The use of CPAP also reduces traffic accidents^7^ and other work-related injuries, and improves work productivity.^8^ Although CPAP therapies are highly effective in normalising AHI and reducing symptoms in symptomatic patients, treatment success is limited by long-term non-adherence in nearly half of patients.^9^ Technical progress in the systems and interfaces (soundproofing, improved masks, humidification, pressure modulation, etc) have unfortunately not been sufficient to improve compliance.^10 11^ Equally, the effect sizes of telemedicine approaches are not as large as what has been achieved with the use of behavioural therapies, and the impacts on patient and provider satisfaction and cost-effectiveness are not yet clear.^12–15^

Non-adherence is related to users’ profiles, their representations of OSAS and the benefits they experience from CPAP.^12 16 17^ This is why cognitive-behavioural and motivation enhancement therapies conducted by health professionals could be effective in ensuring adherence to CPAP. A Cochrane review in 2014 showed that there is a low level of evidence that such interventions increase CPAP use (by 1.44 hours per night in six studies; n=584) and increase the number of participants who used their devices for longer than 4 hours per night (from 28% to 47% in three studies; n=358).^18^ More robust studies are thus needed to increase the level of evidence regarding these types of interventions.

In addition, patient and public involvement (PPI) is more and more advocated in the fields of health education and research.^19–25^ Nevertheless, the efficacy of PPI remains to be demonstrated.^26^ To our knowledge, only one previous pilot study in 39 patients showed that one-to-one peer support at CPAP initiation was feasible and generated high patient satisfaction. However, the study was not powerful enough to demonstrate effectiveness in terms of adherence to CPAP.^18 27^ The data from the study, are, however, useful for designing further studies.

The aim of this adequately powered randomised clinical trial is therefore to assess the role of trained patient involvement (PI) representatives to help patients with OSAS to restart CPAP after discontinuation.

## Methods and analysis

### Study design

This is a prospective, multicentre, randomised controlled trial that will be coconducted by health professionals, a CPAP home provider and patients as experts or peers or participants. After signing a consent form, patients’ participants will be randomised 1.1 to the intervention group with peers or the control group. Nota bene: the peers involved in the conduct of the study will sign a confidentiality agreement of non-divulgation of the information exchanged with the participants.

### Objectives

#### Primary research aim

The primary aim is to evaluate the impact of a 6-month intervention involving trained PI representatives to promote the resumption of CPAP in patients who have discontinued its use.

#### Primary research outcome

Resumption of CPAP is defined as the medical prescription and the setting up of a new CPAP device at home by the homecare provider.

#### Secondary research aims

To evaluate the impact of the peer-driven intervention on adherence to CPAP by comparing adherence with the control group (mean adherence and % of nights with at least 4 hours’ use /night for 70% of nights).To determine the factors associated with the resumption of CPAP treatment.To assess the satisfaction of the intervention group with the peer-driven intervention at 6 months.To evaluate the feasibility and the execution of the peer-driven intervention and the satisfaction of peers after the interviews conducted.

#### Secondary research outcomes

Average adherence to CPAP will be measured from data recorded by the built-in software of the CPAP devices (via tele monitoring or retrieved by a home technician) for 1 month after the final consultation.The relationship between the variables below and a positive response to the peers intervention (defined by a restart of CPAP treatment) will be analysed: age, gender, body mass index, marital status and number of young children (<10 years) education level, socioprofessional status, fragility and social precariousness (using the EPICES score), smoking and alcohol use, comorbidities (using Charlson score), history of OSAS (date of diagnosis of OSAS, baseline AHI), observance to treatments (Girerd score), date and reason for stopping CPAP and EDS score (using the Epworth Sleepiness Scale). To determine patient profiles, their representations of OSAS, their experiences with CPAP and their knowledge and confidence to manage their health, three questionnaires will be completed at inclusion (M0) and at the 6-month follow-up (M6): the Functional Outcomes of Sleep Questionnaire a disease-specific quality of life questionnaire,^28^ the patient activation measure a measure that assesses patient knowledge, skill and confidence for self-management^29^ and the Self-Efficacy Measure for Sleep Apnoea^30 31^ a tool with strong psychometric properties that identifies patient perceptions that may indicate those most likely not to adhere to treatment.The satisfaction of participating patients with the PI intervention and the satisfaction of PI representatives will be measured on a 4-point Likert scale: very dissatisfied, dissatisfied, satisfied, very satisfied.The feasibility and the execution of the three interviews will be assessed by the number of interviews carried out in their entirety and the average duration of each interview (in minutes).

All information will be collected in secure electronic medical records in accordance with the requirements of general data protection regulation.

### Patients

Adults with an established diagnosis of severe OSAS (AHI >30 events/hour) who have discontinued CPAP by returning their device to the homecare provider within 4–12 months after CPAP initiation will be recruited according to the study flow chart depicted in figure 1 (table 1).

**Figure 1 F1:**
[figure not shown]
Study design. CPAP, continuous positive airway pressure; PI, patient involvement; PPI, patient and public involvement. e-CRF, electronic-Clinical Record Form.

**Table 1 T1:** Inclusion and exclusion criteria

Inclusion criteria	Exclusion criteria
Over 18 years old Diagnosed with of severe OSA (AHI ≥30 events/hour) Discontinuation of CPAP 4–12 months after initiation, despite the interventions of health professionals and provider, and having stopped their CPAP treatment no later than 1 year prior to their inclusion Followed by the home healthcare provider AGIRa*Dom.* Access to a computer and/or tablet and an internet connection. Oral and written French. Able to provide written informed consent. Affiliated to social security or beneficiary of such a scheme.	CPAP cessation due to a resolution of the OSAS (eg, weight loss after bariatric surgery) or another pathology that prevents the continuation of treatment (eg, ENT surgery). Severe and/or unstable comorbidity that required hospitalisation for decompensation in the previous year (heart, kidney, respiratory, liver, psychiatric or other insufficiency). Central sleep apnoea index above 20% of AHI at the time of diagnosis Patient being treated with a mandibular advancement orthosis. Lack of availability (eg, night worker or patient who travels frequently). Current participation in, participation in the month prior to inclusion in another clinical intervention research study that may impact the study: this impact is left to the investigator’s discretion. Referred to in Articles L1121-5 to L1121-8 of the socio-professional class (corresponds to all protected persons: pregnant woman, breastfeeding mother, person deprived of liberty by judicial or administrative decision, person subject to a legal protection measure).

AHI, Apnoea–Hypopnoea Index; CPAP, continuous positive airway pressure; ENT, ear, nose, throat; OSA, obstructive sleep apnoea; OSAS, obstructive sleep apnoea syndrome.

### Interventions

#### Recruitment and training of PI representatives

PI representatives will be recruited from the investigators clinics. To be recruited as a PI representative, patients should:

Have used home CPAP for at least 1 year.Have a CPAP adherence of at least 4 hour/night for 70% of nights.Express their motivation in participating in a training and orientation session conducted by research staff and including expert patients from the Grenoble Alpes University Department of Patients (DUP GA).^23^Accept to conduct three motivational sessions by videoconference meetings of 45–60 min duration with 5–8 patients within 6 months after each patient’s inclusion.

Patients with any major psychiatric illness, shift workers or frequent out of town travellers will not be recruited as peers.

Peers will be trained during a three half-days interactive session organised by DUP GA, with experts in patient therapeutic education and communication, and investigators.^23^ Peers will be taught how to interact with the patients recruited in the study: the aim is for them to share their experiences but not to provide any medical advice.

#### Description of the intervention

Trained peers will meet patients randomised into the intervention group by videoconference. Each PI representative will be allocated 5–8 patients. They will conduct three face-to-face motivational sessions, each of 45–60 min duration, over a 6-month period based on the principle of motivational enhancement and cognitive-behavioural therapies.^11 13^ The content of the first session is designed to identify and understand the underlying reasons for stopping CPAP treatment and to identify difficulties encountered by the patient (advantages and disadvantages of CPAP treatment). The aim of the second session will be for the patient to define his/her objectives and priorities. During the last session, will be discussed to strengthen the motivation to change and how to plan for it. The peers will receive €100 per patient for the three interviews.

In the control group, patients will be informed, at inclusion, that they can have a visit with a physician investigator at any time to resume treatment if they wish, as is usual practice. At the end of the 6-month follow-up period, all patients in both groups will have a consultation with their physician who will suggest they resume CPAP treatment. This visit may take place earlier if the patient wishes to resume CPAP treatment before the end of the follow-up period. We planned to start inclusions by November 2021 and end the study by December 2023.

### Statistical analysis

#### Sample size

We hypothesise that 20% of patients allocated to the intervention group will reuse CPAP 6 months as compared with 6% of patients in the control group. A two group χ² test with a 5% two-sided significance level will have 80% power to detect such difference between the two groups when the sample size in each group is 90 (nQuery V.8, Statistical Solutions, Cork, Ireland). In order to take into account a possible drop-outs and to comply with the intention-to-treat principle, we will inflate the sample size by a factor of 15%.^32^ We, thus, plan to include 104 patients per group (ie, 208 patients in total). Fifteen patient peers will be involved.

#### Feasibility and recruitment

The home care provider, *AGIR* à dom. follows more than 20 000 patients with OSAS who use CPAP in the south of France. In 2018, out of 3281 patients who started CPAP within the study area (Isère, Savoie and Haute-Savoie), 365 discontinued it between 4 and 12 months postinitiation and 6% resumed use within 6 months after discontinuation.

#### Randomisation

After consent, randomisation will be performed by a centralised computer software for each investigating centre. It will be stratified on the centre.

### Statistical analysis plan

#### Descriptive analyses

Continuous variables will be expressed as medians (25th/75th percentiles) or means (SD) depending on normality which will be assessed with the Shapiro-Wilk test. Categorical variables will be reported as absolute numbers and percentages for both groups. Baseline comparisons between groups will be made using a Student’s t-test or Mann-Whitney U test, depending on the distribution. For discrete variables, a χ^2^ test will be used. If significant differences are observed between arms, analysis of variance and multivariable regression will be performed. In the case of missing data, an imputation strategy will be applied according to the percentage of missing values. Data management and statistical analyses will be performed using SAS, V.9.4, SAS Institute.

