#### Primary outcome analysis

The impact of the PI intervention on the resumption of CPAP treatment will be studied by comparing the resumption of CPAP in the two arms, using a χ^2^ test. To take into account a possible centre effect, a second analysis will be carried out using a conditional logistic regression stratified by the centre; the intervention or control arm will be considered as the dependent variable.

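### Adjusted models are triggered by significance tests on baseline variables, so covariates would be chosen by chance imbalance rather than by prognosis, and the standing of the resulting estimate is not stated

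*Protocol article*

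**What the plan says.** The rule is in the Protocol article, Statistical analysis plan, Descriptive analyses. For continuous variables: "Baseline comparisons between groups will be made using a Student’s t-test or Mann-Whitney U test, depending on the distribution". For the rest: "For discrete variables, a χ^2^ test will be used". The next sentence makes further modelling depend on the outcome of those tests: "If significant differences are observed between arms, analysis of variance and multivariable regression will be performed".

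Four other places bear on it.

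- **Study design:** patients "will be randomised 1.1 to the intervention group with peers or the control group". Under Randomisation the only stratification factor is centre: "It will be stratified on the centre".
- **Primary outcome analysis:** the primary comparison is fixed without any condition, as "comparing the resumption of CPAP in the two arms, using a χ^2^ test". To allow for a centre effect, "a second analysis will be carried out using a conditional logistic regression stratified by the centre". Neither analysis names a prognostic covariate.
- **Secondary outcomes analyses:** mean compliance has a fixed mixed model with arm and centre. The regressions that do use baseline variables look for factors associated with resumption, which is a different objective.
- **Secondary research outcomes:** this section lists the baseline variables to be collected, starting with "age, gender, body mass index, marital status and number of young children (<10 years) education level, socioprofessional status".

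**The concern.** A significance test of a baseline variable between randomised arms asks whether the difference could be due to chance. If allocation worked, the answer is known in advance: it is. A small p-value then says nothing about whether the variable matters for the outcome, yet here it decides whether an adjusted model is fitted.

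Three consequences follow.

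- **Wrong selection criterion.** A strong predictor of resumption that happens to be balanced is left out, although adjusting for it would add precision. A variable unrelated to resumption that happens to be imbalanced prompts adjustment.
- **Unclear standing.** The sentence names no outcome and no list of covariates. It does not say whether the triggered model adds to the analyses under Primary outcome analysis or how it ranks against them. Analysis of variance suits a continuous outcome, whereas the primary outcome is binary, so the intended target cannot be inferred from the method.
- **No cap on covariates.** Few events are expected, and the rule does not limit how many variables may enter.

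At stake is a further treatment-effect estimate whose existence and content depend on the data, and which readers could not rank against the planned ones.

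**Working it through.** **1. The plan's own figure.** Inputs from Sample size: 20% versus 6%, two-sided 5%, 80% power, 15% inflation. With pooled variance and no continuity correction, and mean proportion (0.20 + 0.06)/2 = 0.13:

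n = [1.960·√(2·0.13·0.87) + 0.842·√(0.20·0.80 + 0.06·0.94)]² / 0.14² = (0.932 + 0.392)² / 0.0196 ≈ 89.4, so 90 per group.

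90 × 1.15 = 103.5, so 104 per group. The stated 90 and 104 reproduce, and nothing below changes them.

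**2. Expected events.** 104 × 0.20 + 104 × 0.06 = 20.8 + 6.24 ≈ 27, if all 208 patients contribute an outcome.

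**3. Number of baseline variables.** Secondary research outcomes lists 17 characteristics by my count: age, gender, body mass index, marital status, young children, education, socioprofessional status, EPICES, smoking, alcohol, Charlson, date of diagnosis, baseline AHI, Girerd, date of stopping, reason for stopping, Epworth. Three questionnaires at M0 make 20. Descriptive analyses does not say which of these are tested, so a range of 10 to 20 is used.

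**4. How often the trigger fires.** The level of the baseline tests is not stated; 5% is assumed, with independent tests. The chance of at least one significant difference among k variables is 1 − 0.95^k.

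| k | Chance of trigger | Expected number significant |
|---|---|---|
| 10 | 40% | 0.5 |
| 18 | 60% | 0.9 |
| 20 | 64% | 1.0 |

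**5. Effect on power.** Covariate strengths are assumptions, not taken from the documents. All logistic tests are Wald tests with 104 per arm.

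*Simulation A:* 18 independent covariates, one prognostic, 3,000 trials per scenario. The control rate is 6% and the within-covariate odds ratio is (0.20/0.80)/(0.06/0.94) = 3.92, so the overall intervention rate falls somewhat below 20%, more so with the stronger covariate. The trigger fired in about 61% of these trials.

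*Simulation B:* 20 covariates, four prognostic (log odds ratio 0.5 per SD), about 21% versus 6%. The prespecified model uses three prognostic covariates.

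| Setting | No adjustment | Triggered | Prespecified |
|---|---|---|---|
| A, log OR 0.7 per SD | 80.1% | 80.5% | 82.6% |
| A, log OR 1.0 per SD | 75.2% | 74.4% | 79.9% |
| B | 87.6% (χ²) | 86.5% | 89.0% |

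Prespecification gains 82.6 − 80.1 = 2.5, 79.9 − 75.2 = 4.7 and 89.0 − 87.6 = 1.4 points over no adjustment. Triggered adjustment changes power by +0.4, −0.8 and −1.1 points. For scale, the Monte Carlo standard error of one power figure in A is about √(0.8·0.2/3000) = 0.7 points.

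**6. Effect on type I error.** The exact rejection rate of the χ² test with no treatment effect is 4.8% at a 6% event rate and 5.1% at 13%. Simulation B with no effect (4,000 trials):

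| Event rate | χ² | Logistic, no covariates | Triggered | Prespecified |
|---|---|---|---|---|
| About 6% | 4.8% | 3.7% | 4.0% | 3.5% |
| About 12% | 5.1% | 4.4% | 4.9% | 4.6% |

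In A, taking the better of the unadjusted and triggered results gave 3.6% to 3.8% at a 6% event rate and 4.8% to 5.1% at 13%.

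**The case against.** The strongest reply is that no stated primary or secondary result depends on the rule. The χ² test and the centre-stratified second analysis are fixed unconditionally, as is the compliance model. The sentence sits among the descriptive analyses and nowhere says that its models replace anything. This stands, and it limits the point to additional analyses. It does not remove the point: a regression triggered by between-arm tests is not descriptive, and its placement makes its purpose harder to read.

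A reader might infer that the trial's test loses its nominal 5% level, or that rejection rates below 5% under the triggered rule show power lost to it. The documents and the check do not support either. The χ² test stays at about 5%. The low rates in the logistic models appear equally with no covariates and with prespecified ones, so they reflect the conservatism of Wald tests with few events.

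Two further objections also stand in part. The 64% requires 20 independent tests, and related scales such as Epworth and the sleep quality-of-life questionnaire are unlikely to be independent. And forgoing adjustment is not an error, because an unadjusted primary test is valid.

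It could finally be said that a separate analysis plan will settle the matter. That would answer an omission. Here the protocol states the rule outright.

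**Conclusion.** The point holds as a criticism of a stated rule with limited reach. Baseline significance tests between randomised arms are the only stated trigger for these adjusted models, so the covariates would be selected by chance imbalance. Neither the target outcome nor the standing of the models is given.

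The trigger would be a common event: about 40% of trials with 10 variables and 64% with 20, assuming independent tests at 5%. Positive correlation among the variables would lower these figures.

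The primary χ² test, its type I error and the sample size are unaffected. The cost is a data-driven additional estimate of unclear standing, plus about 1 to 5 power points of forgone precision. That range depends wholly on assumed covariate strengths. The triggered rule itself made little difference to power compared with no adjustment.

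**What to change.** Under Descriptive analyses, delete the baseline significance tests and the conditional sentence, and state that baseline characteristics will be summarised by arm without testing. Leave the χ² test under Primary outcome analysis as the primary analysis.

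If an adjusted analysis is wanted, add one sentence there: resumption will also be modelled with arm and two or three named M0 covariates, stratified by centre, whatever the observed balance, as a supportive analysis. Name the covariates before any outcome data are seen, choosing from variables already collected and on expected prognostic value. The documents list those variables as factors to explore and do not show which of them predict resumption, so the choice needs the investigators' justification.

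The cost is wording only: no new data, no change to the 104 per group. The small downside is that the covariates must be few, since only about 27 events are expected, and the choice cannot be revisited once data are seen.
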